**Title: BRIDGE: Linking People who Inject Drugs to HIV Testing and Care**  
**Abbreviated Title: BRIDGE**  
**Principal Investigator: [name]**

## **BRIDGE** **Stand-Alone Protocol for Effectiveness Outcomes**

### **1. STUDY DESCRIPTION**

#### *Background: HIV and injection drug use in Kazakhstan*

An estimated 1% of Kazakhstani adults (N=122,850) inject drugs. In some cities along drug trafficking routes, the rate is as high as 14%, representing one of the highest injection drug use rates in the world. As the epidemics of heroin use and HIV spread across Central Asia, there is an urgent need to scale up low-threshold highly effective HIV services for people who inject drugs (PWID) in needle & syringe programs that may be integrated with HIV care to curb HIV transmission. Cities selected for this study - Almaty, Karaganda, Temirtau, and Shymkent - are geographically disparate and HIV prevalence rates among PWID range from 7% to 21%. Total populations range from 145,000 to over 1.5 million, which will ensure greater generalizability of study findings.

Major gaps in the HIV care continuum from HIV testing to virologic suppression among Kazakhstani PWID (see Figure 1) mirror gaps found among injection drug use driven HIV epidemics in Central Asia, Eastern Europe, and Asia. Only 4% (N=935) of the estimated 19,000 PWID living with HIV/AIDS in 7% of the registered 12,574 HIV-positive cases in Kazakhstan achieved viral suppression in 2014 as shown in Chart 1. This steep drop in the continuum of care among PWID is consistent with research worldwide among PWID HIV-positive PWID who remain untreated and viremic play a major role in increasing the epidemic in their communities. Research suggests that, if offered the opportunity to be on ART, PWID are equally as likely to benefit from it as people living with HIV/AIDS who do not inject drugs. ART initiation among PWID is associated with significant subsequent reductions in HIV incidence, unprotected sex and unsafe injections. This research highlights the critical importance of identifying and linking or relinking PWID living with HIV to HIV care with an ultimate aim of initiating ART and virologic suppression. Currently 5,579 HIV-positive PWID with CD4 counts <500 will newly qualify for ART in Kazakhstan and need to be linked or relinked to HIV care to initiate ART.

Worldwide, needle & syringe programs (in Kazakhstan, more commonly known as Trust Points) have played a pivotal role in curbing the HIV epidemic by providing HIV prevention information along with syringes and condoms, and referring PWID to HIV testing and treatment. A recent meta-analysis of 12 studies with 12,000 person years found that Trust Points (TPs) significantly reduced the likelihood of HIV transmission with a pooled effect size of 0.66. TPs across Kazakhstan represent the largest single type of service provided to PWID, dwarfing opiate substitution treatment (OST) and other drug treatment services. Kazakhstan contains over 140 TPs, all of which are located in "Trust Points", which also provide services to commercial sex workers, men who have sex with

**Figure 1: HIV Care Cascade for PWID in Kazakhstan**

[figure not shown]

men, and other high-risk groups. All trust points in Kazakhstan are regulated by the Republican AIDS Center. Estimates of TP coverage of PWID (at least one visit to a TP in the past year) in Kazakhstan range widely between 10%-47%. Mathematical modeling from a meta-analysis of TPs suggests that increasing coverage of TPs to 50% of PWID could reduce HIV incidence rates by 20% after 5 years and linking 50% of HIV-positive PWID with CD4 counts <500 to ART could result in a 20% decrease in the HIV incidence rate.

### *1.1. STUDY PURPOSE*

The main aim of the proposed study is to increase linkages to care by evaluating the effectiveness of implementation, feasibility of expansion, and sustainability of an enhanced integrated HIV service package (BRIDGE) for Trust Points (TPs), also known as Needle Syringe Programs or Harm Reduction Programs for PWID) that includes low-threshold strategies of peer-driven recruitment, HIV counseling and testing (HCT), and ARTAS (CDC's recommended case management strategy to link PWID to HIV care) delivered by TP case managers who will be trained and supervised by TP nurses.

The BRIDGE intervention is systematically designed for PWID to address specific service barriers to HIV testing, and link them to HIV care and promote ART initiation. BRIDGE is an integrated intervention which combines the following three components: (1) Social Network Strategy (SNS), a peer-driven recruitment approach, which has demonstrated effectiveness in reaching hidden and hard to reach populations of unknown HIV status and successfully linking them to HIV testing; (2) HIV Counseling, Testing, and Referral (CTR), adhering to WHO and CDC guidelines for confidential, HIV Rapid Testing conducted by AIDS center nurses and accompanying confirmatory test; and (3) ARTAS, an evidence-based case-management intervention to link recently-diagnosed HIV-positive persons to care and retain them in care. The study builds on the investigative team's decade-long HIV intervention research with PWID in Kazakhstan carried out in collaboration with the Republican AIDS Center (RAC). It addresses implementation research questions to improve HIV service delivery systems for PWID that are not only important to the region, but have relevance for the 120 countries that have concurrent injection drug use and HIV epidemics. This study will employ an innovative design to evaluate implementation and effectiveness of BRIDGE on improving linkage to HIV care and initiation of ART in 24 TPs located in 4 geographically diverse Kazakhstani cities using a stepped wedge trial and site-level data collected from TPs and AIDS centers.

### *1.2. STUDY AIMS*

Specific aims for the proposed research are:

#### **Primary Aims**

**Aim 1:** To evaluate the effectiveness of implementing BRIDGE's enhanced service integration approach in increasing number of PWID who are tested for HIV in TPs, and improving linking HIV-positive PWID to HIV care (primary outcomes).

#### **Secondary Aims**

**Aim 2:** To evaluate the effectiveness of BRIDGE's enhanced service integration approach on increasing retention in AIDS center, initiating ART, and increasing adherence to HIV treatment regimens and virologic suppression;

**Aim 3:** To assess how multi-level theory-driven factors (client, staff, agency, community, structural) influence the implementation and effectiveness of BRIDGE on Aim 1 and Aim 2 outcomes; and

**Aim 4:** To evaluate the implementation process and cost of BRIDGE including implications for cost-effectiveness, feasibility of expansion, and sustainability.

### *1.3. STUDY RATIONALE*

Scaling up integrated, cost-efficient HIV services for people who inject drugs (PWID) in Needle Syringe Programs (TPs) is urgently needed in Kazakhstan, where only one-third of the estimated 19,000 HIV-positive PWID are ever linked to HIV care and only 10% initiate ART. The study's aim is to evaluate the implementation, effectiveness, and sustainability of an integrated HIV service model in 24 TPs in 4 cities that includes highly effective strategies of peer-driven recruitment of PWID using social network strategies (SNS), rapid HIV testing and counseling in TPs, and linkage of HIV positive PWID in TPs to HIV care using the ARTAS case management model. Findings will have important public health implications for improving HIV service delivery for PWID in the Central Asian region

and other countries with injection driven epidemics.

## **2. STUDY DESIGN & STATISTICAL PROCEDURES**

The proposed study will evaluate the implementation and the effectiveness of the enhanced service integration approach of BRIDGE in trust points via a stepped wedge trial. A stepped wedge trial is a novel type of cluster trial design that is increasingly being used to evaluate service intervention. In a stepped wedge design there are random and sequential crossover of clusters from control to intervention until all clusters are exposed.

There are three main components to the study that are referred to throughout this protocol, each with their own sets of procedures and participants. The first is the BRIDGE intervention itself, described directly below and in the Intervention Manual included in this submission. As an implementation study, the BRIDGE team will train existing service providers to deliver this intervention to PWID at trust points in four study sites. Trust point staff will enroll PWID in each element of the intervention. We estimate that BRIDGE has the potential to reach up to 557 PWID per trust point (for a total of 13,381 PWID). Process measures, an electronic barcode-based tracking system known as AppSheet (described in Appendix A to this protocol), and medical records review referred to as the AIDS Center Semi-Annual Report (described in Appendix B to this protocol) will be used to assess outcomes from this study component.

### *2.1. OVERVIEW OF BRIDGE INTERVENTION*

BRIDGE is an integrated intervention which combines the following three components: (1) Social Network Strategy (SNS), a peer-driven recruitment approach, guided by network theory which has demonstrated effectiveness in reaching hidden and hard to reach populations of unknown HIV status and successfully linking them to HIV testing as well as re-engaging HIV-positive PWID who never initiated or were never retained in care; (2) HIV Counseling, Testing, and Referral (CTR), adhering to WHO and CDC guidelines for confidential, HIV Rapid Testing conducted by AIDS center nurses and accompanying confirmatory test; and (3) ARTAS, a strengths-based case-management intervention to link recently-diagnosed HIV-positive persons to care and retain them in care. SNS, CTR, and ARTAS components have proven to be highly effective strategies used in many countries, including numerous studies by co-investigator [name] and have been refined by the investigative team to enhance cultural relevance with Kazakh and Russian themes that emerge from focus groups and mapping surveys). The three components will be packaged and presented as one intervention. A more detailed description of Bridge and each intervention component is provided in the Bridge Intervention Manual.

### *2.2 STUDY DESIGN*

Bridge will be implemented in four cities, in Kazakhstan: Almaty, Shymkent, Temirtau & Karaganda. Due to their geographical proximity of Temirtau and Karaganda, and overlapping administration of HIV clinics they will be considered as one “site” for intervention roll out. In month 16, we will use computer software to sequentially randomly assign the three sites six months prior to implementing BRIDGE in months 22, 28 and 34.

We opted for a stepped wedge trial over a cluster RCT for ethical reasons so that all clusters will eventually receive the intervention as well as to avoid contamination and to be able to control for exogenous time specific effects as discussed earlier. The unit under experimental control will be a city, with the timing of roll-out of BRIDGE in each of the study’s cities—Almaty, Shymkent Karaganda, and Temirtau—to be randomly assigned. Since the cities are geographically disparate (with the exception of Karaganda and Temirtau, which is why we will consider them as a single study site) the likelihood of participant contamination is minimal.

The stepped wedge approach represents a scientific alternative to the randomized control trial (RCT) by providing a valid counterfactual to evaluate the impact of BRIDGE compared to the TP Standard of Care. This roll out design also more closely resembles the method of implementing BRIDGE in a real-world setting. The use of multiple groups and our data analytic plan will allow us to control for exogenous time-specific effects, such as introducing new HIV initiatives or funding cuts and minimizes contamination as all TP sites in a city will receive BRIDGE at the same time. More importantly, this design addresses important ethical considerations of communities by ensuring that all TP sites will eventually receive BRIDGE, which is a potentially lifesaving intervention.

The following figure describes the stepped-wedge rollout of Bridge in the four cities (with Karaganda & Temirtau combined as one study site):

Figure 2: Stepped Wedge Design

[figure not shown]

### 2.3. PROPOSED CONCEPTUAL FRAMEWORK FOR STUDY

The study is guided by the diffusion of innovation theory and implementation research, which identifies key multi-level factors that enhance or diminish implementation fidelity and the effectiveness of intervention delivery. We have identified the Conceptual Framework for Implementation Research (CFIR) as a guiding framework for our intervention. The CFIR framework consists of five distinct domains, each with a number of constructs serving as sub-domains (see Figure 3).

Figure 3: Conceptual Framework Guiding Implementation

[figure not shown]

The study uses this innovative conceptual framework and employs mixed methods to identify with greater depth and precision multi-level factors (i.e. clients, staff, organization, and structural factors) which are hypothesized to influence the fidelity of implementation, effectiveness, and sustainability of BRIDGE. This mixed methods study will inform dissemination strategies to best promote the uptake and sustainability of BRIDGE in TP settings, if found to be effective.

### 2.4. STUDY ANALYSES

#### *Data analyses by study aim*

To test Aim 1 hypotheses, we will compare data on service linkage outcomes during post-intervention to service linkage outcomes during pre-intervention. Data for Aim 1 will be obtained from the AppSheet tracking system and process measures on ARTAS sessions.

For Aim 2, we will compare data on HIV testing in TPs, retention in HIV care, ART initiation, ART adherence, and viral suppression during post-intervention to these same data during pre-intervention. Data for Aim 2 will be obtained from the AppSheet tracking system and the AIDS Center Semi-Annual Report.

| Table 1: Measurement of Study's Outcome Variables           |                                                                                    |                                            |                                                 |
|-------------------------------------------------------------|------------------------------------------------------------------------------------|--------------------------------------------|-------------------------------------------------|
| Variable                                                    | Instrument/Measure                                                                 | Time point(s) a                 | Source                                          |
| Program Data                                         |                                                                                    |                                            |                                                 |
| PRIMARY OUTCOME: HIV-positive TP clients accessing HIV care | # and % of HIV-positive clients who visit HIV clinic $\geq 1$ time in past 90 days | Ongoing (checked quarterly)                | AppSheet tracking system                        |
| HIV-positive TP clients retained in HIV care                | # and % of HIV-positive clients who visit HIV clinic $\geq 3$ time in past 90 days | Ongoing (checked quarterly), semi-annually | AC semi-annual report, AppSheet tracking system |
| HIV testing at TP                                           | # and % of TP clients who have received an HIV test at TP                          | Ongoing (checked quarterly)                | AppSheet tracking system                        |
|                                                             | # of TP clients seen                                                               | Ongoing (checked quarterly)                | AppSheet tracking system                        |

Statistical Analysis for Aims 1 and 2: Descriptive analyses include the overall frequencies and distributions as well as estimates of parameters of interest such as measures of central tendency, dispersion, and their standard errors. These analyses also ensure proper application of the analytic procedures used to test hypotheses (e.g., distributional assumptions are met, potential outliers).

Analysis of Program data: Formal hypothesis testing based on program data will test for differences in outcome measures obtained during the pre-intervention period (i.e., time points before BRIDGE is implemented in a city) versus periods when BRIDGE is implemented. We will employ permutation tests (a.k.a. “randomization tests”) for significance testing because of concerns that the distribution of measures may not be approximated well by a small sample size (i.e.,  $N=24$  TPs). In experimentally controlled trials with small sample sizes, permutation tests have been shown to be superior to parametric tests. As a heuristic and non-parametric approach, permutation testing more accurately estimates the nominal type I error rate for cluster randomized clinical trials with small sample sizes and with measures that may not be normally distributed compared to candidate parametric procedures. Strong hypothesis testing in this manner involves permuting the BRIDGE implementation status of each time point; since the time period “assignment” (pre-implementation vs. BRIDGE) is allocated based on city, permutations will account for clustering by city (i.e., a permutation for TPs in the same city will all be assigned the same implementation status for that time point). Not only does this conservatively account for shared variance that might be present due to being located in the same city, statistical efficiency can be improved by clustered permutation testing. For inference, the test statistic (difference in means) observed based on actual period assignments is compared vis-à-vis the distribution of test statistics using permuted assignments, with the proportion of permuted test statistics greater than the actual observed taken as the one-sided or half of the two-sided p-value. With program measures collected quarterly over 42 months, the number of clustered permutations with 3 study sites (4 cities) is 38,416, allowing testing of statistical significance with  $\alpha < .0001$ . If we permute all 24 TPs independently, tests of significance can be performed with much lower  $\alpha$ . We will conduct both permutation tests with sites permuted independently as well as clustered permutations by city and report the result with the more conservative p-value. Hypothesis testing for Aims 1 and 2—i.e., estimating the effectiveness of the intervention—will involve

examination of the population-level effect in the statistical models to make inferences about the treatment effect.

Power analyses for Aims 1 and 2: Estimates of power to detect significant differences for each hypothesis was conducted. Power analyses were conducted using G\*Power (v3.1.0), two-tailed hypothesis testing, and  $\alpha=.05$ ; results are presented separately for site level data (Figure 3). For site level data, the smallest effect size for Aims 1 and 2 proportion achieving undetectable viral load; power analyses for this “rate limiting” effect size used unconditional exact test to simulate permutation testing method of estimating p-values as well as simulated cluster permutation (i.e., TPs in a city covary together). The autocorrelation and clustering effects were modeled as overall “intraclass correlation” (ICC), using a range of ICCs observed in our prior studies. Results indicate 80% power is achieved with a sample size of 24 TPs (Figure 4).

[figure not shown]

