### 3.6. BRIDGE DATA COLLECTION

A summary of all sources of data collection is provided in the table below.

Table 2: BRIDGE Data Sources

| Name                    | Description & Purpose                                                         | Source                                                           | Identification of Data                                                                               | Pre-intervention         | Post-intervention                                                    |
|-------------------------|-------------------------------------------------------------------------------|------------------------------------------------------------------|------------------------------------------------------------------------------------------------------|--------------------------|----------------------------------------------------------------------|
| Process measures | Assess fidelity of BRIDGE implementation, for use in QA                       | Paper forms completed by BRIDGE TP nurses & OWs                  | Data identified by trust point, only aggregate data, no PHI or other sensitive information collected | n/a (not collected)      | Forms completed, collected and reviewed monthly by site coordinators |
| CFIR Surveys     | Assess implementation climate & organizational culture of BRIDGE trust points | TP, AC and RAC staff who are involved in the BRIDGE intervention | Data identified by study-assigned ID code                                                            | Every 6 months           | Every 6 months                                                       |
| AppSheet System  | Short surveys to assess services                                              | Filled out by TP and AC                                          | All PWID clients given                                                                               | Continuous collection of | Continuous collection of                                             |

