## **6. CONFIDENTIALITY OF STUDY DATA**

Human subjects' protection and data safety remain an utmost priority. The primary risks are (1) psychological discomfort and/or distress arising from the personal and potentially sensitive nature of information elicited during assessments; and (2) loss of confidentiality. The level and probability of experiencing such risks are minimal, and the monitoring plan described below is commensurate with these risks. There will be ongoing monitoring of the conduct of the trial to ensure that there are no undue risks to participants, and the data are being collected in a valid and reliable way. In addition, Drs. [name], [name], and the project director are directly responsible for monitoring the security of the data and the safety of participants. Approval will be received from the Columbia University IRB and the Ethics Committee of the Kazakhstan School of Public Health prior to the start of the study.

Safeguarding the confidentiality of personal data reported in screening questionnaires will be achieved via use of instruments that do not contain identifying information as defined by the Health Insurance Portability and Accountability Act (HIPAA).

RAs will verify that all screening instruments and answer sheets are gathered before they leave the data collection site. Safeguarding of program-level primary outcome data on TP clients collected through recruitment coupons and service referral vouchers will use anonymous alphanumeric codes that are not linked to any client data and will be used to generate summary statistics on overall number of TP clients recruited and number of HIV positive clients linked to HIV Care Clinics.

All hardcopy items with identifying information (e.g. brief contact information collected during screening, locator forms, biotesting release form required by the AIDS Center) will be kept in a locked file cabinet in the Project Director's office. All software files with identifying information will be stored on a computer protected by passwords and a firewall; backup copies of files will be encrypted and password protected using 128-bit AES encryption before being archived in a locked file cabinet in the Project Director's office.

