## Data Analysis Plan for Primary Study Aim

### Hypothesis:

Compared to pre-implementation time blocks, time blocks where Bridge is implemented will have increased numbers of PWID clients who (a) attend NSPs, (b) receive a rapid test for HIV at NSPs, and (c) link to HIV care at the AIDS center, when their test is positive for HIV care in the past 6 months)

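### The plan names one, two or three primary outcomes depending on the section, gives conflicting data sources for linkage, and states no multiplicity rule

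*Combined protocol and SAP*

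**What the plan says.** **Which outcome is primary**

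- Section 1.2, Primary Aims, has two: "increasing number of PWID who are tested for HIV in TPs, and improving linking HIV-positive PWID to HIV care (primary outcomes".
- Table 1 in Section 2.4 labels a single row: "PRIMARY OUTCOME: HIV-positive TP clients accessing HIV care". It is measured as the number and percentage of HIV-positive clients with at least one HIV clinic visit in the past 90 days. The only source listed is AppSheet.
- The text above Table 1 moves testing to the secondary aim: "For Aim 2, we will compare data on HIV testing in TPs, retention in HIV care, ART initiation, ART adherence, and viral suppression". Appendix A (purpose of AppSheet data collection) does the same, although Aim 2 in Section 1.2 does not list testing.
- The Data Analysis Plan for Primary Study Aim has three counts: clients who attend, clients who are rapid-tested, and clients who "link to HIV care at the AIDS center, when their test is positive for HIV care in the past 6 months". Its formal-testing paragraph bases the primary test on client visits to the needle and syringe programmes.

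**Where the data come from**

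- Section 2.4: "Data for Aim 1 will be obtained from the AppSheet tracking system and process measures on ARTAS sessions". The introduction to Section 2 also lists process measures among the tools for assessing outcomes.
- Section 6 refers to "program-level primary outcome data on TP clients collected through recruitment coupons and service referral vouchers", to be used for totals of clients recruited and of HIV-positive clients linked.
- Table 2 in Section 3.6 gives process measures before the intervention as "n/a (not collected" and their purpose as fidelity and quality assurance.
- The formal-testing paragraph of the analysis plan draws on the app-based system alone.

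**Error control**

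An alpha of .05, two-tailed, is stated only in the power paragraph of Section 2.4. There is no ordering of outcomes, no split of alpha and no statement on whether one or all must succeed.

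**The concern.** A reader cannot tell from the plan which result would mean that BRIDGE worked. The versions differ in number of outcomes, in denominator (all HIV-positive clients, or those who test positive), in window (90 days, or an unclear 6 months) and in scale (number and percentage, or numbers only).

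The source conflict matters more than a normal drafting slip. Coupons belong to the peer-recruitment component that arrives with BRIDGE (Section 3.3), and completed vouchers are logged under ARTAS (Table 3). Process forms start at rollout. Any linkage known only from these sources adds to the implementation periods and nothing to the earlier ones, so the error can only favour BRIDGE.

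An open choice of outcome also leaves room for selection after the data are seen. Section 3.3 lets the study team view AppSheet data as they accrue.

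**Working it through.** The plan gives no figure of its own on this point to reproduce. The stated 80% power concerns viral suppression, which is not primary in any version, and the text gives no effect size or ICC values from which to recompute it.

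**1. The versions side by side**

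| Place | Primary outcomes | Linkage denominator | Window | Scale | Source |
|---|---|---|---|---|---|
| Section 1.2 | 2: testing, linkage | HIV-positive PWID | none given | number tested; linkage not stated | none given |
| Table 1 | 1: clinic visit | HIV-positive TP clients | 90 days | number and % | AppSheet |
| Section 2.4 text | linkage (testing under Aim 2) | none given | none given | none given | AppSheet and ARTAS process measures |
| Section 6 | recruitment and linkage totals | HIV-positive clients | none given | numbers | coupons and vouchers |
| Analysis plan | 3: attend, test, link | those testing positive | 6 months, unclear | numbers | app only |

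**2. Size of one-sided ascertainment, if Section 2.4 or Section 6 were followed**

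Let s be the share of true linkages that AppSheet captures and r the share of the missed ones that BRIDGE-only sources recover. With no true effect, the apparent post/pre ratio is (s + (1 − s)r)/s. Both inputs are assumed, since the documents give neither.

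- s = 0.90, r = 0.25: 0.925/0.90 = 1.03
- s = 0.75, r = 0.50: 0.875/0.75 = 1.17
- s = 0.60, r = 0.75: 0.90/0.60 = 1.50

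If Table 1 and the analysis plan are followed, r = 0 and the ratio is 1.

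**3. Family-wise error, each test at .05**

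- Any one suffices, independent tests: 1 − 0.95² = 0.0975 for two; 1 − 0.95³ = 0.1426 for three.
- Any one suffices, correlated normal statistics (simulation, one million draws): for three tests, 0.125 at rho 0.5 and 0.099 at rho 0.8; for two tests, 0.091 and 0.078.
- All must succeed: at most 0.05.

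**4. Why the scale has to be fixed**

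Section 5 gives 597 clients per TP and 13.3% HIV-positive: 597 × 0.133 = 79.4, about 80. Assume 40 of 80 are linked (50%), and that BRIDGE brings in 40 clients who were out of care. The result depends on the share of those 40 who link:

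- 25% (10): 50/120 = 41.7%, count up 25%
- 40% (16): 56/120 = 46.7%, count up 40%
- 50% (20): 60/120 = 50.0%, count up 50%
- 60% (24): 64/120 = 53.3%, count up 60%

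Count and percentage move in opposite directions only when the new clients link at a lower rate than the existing ones. The count has its own weakness: Appendix A (client enrollment) asks trust points to enrol as many clients as they can throughout the study. AppSheet counts can therefore rise with calendar time, and in a stepped wedge calendar time runs with exposure to BRIDGE.

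**The case against.** The best reply is that the operative text is consistent on source. Table 1's primary row and the formal-testing paragraph both use app data only, and Table 2 shows AppSheet running continuously in both phases. Appendix A places the added post-rollout items in the Trust Point nurse surveys, so nothing shows the AIDS Center items changing. Process forms are aggregate only and meant for quality assurance. Without client IDs they cannot be merged with AppSheet records.

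Much of this stands. A reader might infer that linkage is measured differently before and after rollout. The documents do not establish that; they contain two incompatible source rules, and only one has that effect. The merging argument is weaker: aggregate counts can still be added together, and the codes described in Section 6 carry no link to other client records, so duplicates could not be removed.

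A reader might also infer that several primary tests will each be run at .05 with any one counting as success. That is an inference from silence. The analysis plan joins its three counts with an *and*, which could mean that all must succeed. Independence is also unlikely, because attending, testing and linking are successive steps.

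Finally, one could read the analysis plan as a 6-month look-back checked each quarter, which would mix pre and post exposure at rollout. That joins two separate places. The analysis plan speaks of time blocks and does not say they are quarters, and its 6-month clause is too unclear to show what it governs.

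It is also fair that attendance and testing are different outcomes, not rival definitions of linkage, and that numbers are contained in number and percentage. The scale is under-specified rather than contradictory.

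**Conclusion.** The point holds as a set of conflicts that must be reconciled before analysis. The number of primary outcomes, the status of testing, the window, the denominator and the data source differ between sections, and no text ranks them.

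Bias towards BRIDGE is conditional. It arises if the source rule in Section 2.4 or Section 6 is applied, with an apparent ratio of 1.03 to 1.50 under the assumed capture rates. It does not arise under Table 1 and the analysis plan, provided the AIDS Center items are the same in both phases. The survey forms are not in the documents, so that could not be checked.

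The error inflation is also conditional: 9.8% (two tests) or 14.3% (three) if any one success suffices and the tests are independent, less under positive correlation, and at most 5% if all must succeed. The plan does not say which applies.

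**What to change.** 1. Keep the outcome that Table 1 labels primary: HIV-positive TP clients with at least one HIV clinic visit in the 90-day quarter.
2. Derive it in both phases only from AppSheet AIDS Center records with identical items. Use ARTAS forms, coupons and vouchers for fidelity only.
3. Fix one scale, count or percentage, before analysis and report the other beside it. Either is defensible if the risks shown in step 4 of the working are acknowledged.
4. If testing, or testing and attendance, stay primary, state an alpha rule, for example a fixed sequence or a rule that all must succeed.
5. Bring these places into line: Section 1.2 (Primary Aims), the introduction to Section 2, Section 2.4 with Table 1, Section 6, the purpose paragraph of Appendix A, and both the hypothesis and the formal-testing paragraph of the analysis plan.

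The cost is wording, plus two real losses. Linkages recorded only on ARTAS forms would not be counted. Under a fixed sequence, the later outcomes could be tested only if the first succeeds. An equal split of alpha is a further option but costs power: by normal approximation, a test with 80% power at .05 has Φ(1.960 + 0.842 − 2.241) = 71% at .025 and Φ(1.960 + 0.842 − 2.394) = 66% at .0167.
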